**MOMMY ‐ Epi: Impact of Epigenetic Markers at Birth on Infant Gut Microbiome**
* Interactions between host genetics and gut microbiota reveals microbial signatures that are common and characteristic of complex diseases [57, 58]. However, most current research on the genetic‐microbiome interaction focuses on adults. The gut microbiome of adults is affected by factors such as age, geographical environment, diet, disease, etc. Limited interaction between early life gut microbiome and host genetics was identified in current large‐scale studies. DNA methylation is the most extensively studied epigenetic mechanism, first appearing during cellular differentiation in embryogenesis. A cohort study in the US explored the connections between prenatal exposure, epigenetic alterations, and the development of the microbiome [59]. This study identified a set of CpG sites with modified methylation patterns in the cord blood of infants born to mothers with asthma. These sites were enriched with elements responsive to microbes and were associated with both microbial colonization in the upper respiratory tract at 2 years and the onset of childhood asthma. However, it remains unclear how epigenomic configurations at birth may influence the impact of perinatal factors on the initial establishment and growth of the infant gut microbiome.We are building up a comprehensive integrative early life microbiome platform with the aim to understand the complex host–environment–microbe interactions in microbiome seeding and development in early life. We will focus on the epigenome at birth, a factor that is poorly studied, which controls host gene expression and may partially program gut microbiota development and health outcomes. In MOMMY‐Epi, with an identified core subset of 968 families from the MOMMY inception cohort, we will perform a comprehensive integrative analysis metagenomic sequencing of the maternal fecal samples collected at the third trimester and infant fecal samples collected at birth and 2 months of age, as well 16S and ITS amplicon sequencing for breastmilk samples and vaginal samples. Beyond metagenomics, we will also utilize other omics, including epigenomes of cord blood samples derived from whole genome bisulfite sequencing to provide insight into host factors in this scenario. This project will conduct bioinformatics big data integration on the whole genome/epigenome sequence and intestinal microbiome to characterize how the early life microbiome seeding processes are affected by host genomes and pinpoint the keystone microbiome taxa that lead to healthy gut homeostasis.Integrative analysis of the epigenome, exposome and microbiome in early life will advance our knowledge of the impact of environmental exposures on the interplay between host epigenome and microbiome in early life and associated disease outcomes, hence facilitating the development of integrated omics markers for more precise and sensitive early disease detection. This project will also generate the first single databases that contain comprehensive data on both microbiome from multiple body sites and epigenomes. Such a database will drive and accelerate the new direction of microbiome research and development.(iii)
*
**MOMMY ‐ MAGIC: Establishment of a High‐quality Metagenome‐assembled Genome Inventory**
* During the establishment of the cohort and subsequent analyses on microbiome data in early life, we identified a research gap that early‐life microbiota data are underrepresented in existing databases, hampering accurate profiling of the infant gut microbiome. To address this gap, we generated a Metagenome‐Assembled Genome Inventory for Children (MAGIC) from more than 19,559 early‐life (0–7 years) publicly available early‐life metagenomes in combination with 613 metagenomes generated from our MOMMY inception cohort [60]. In this project, we generated an early‐life gut virome database that will enable complete and accurate profiling of infant/child gut virome. We utilized state‐of‐the‐art bioinformatic tools to generate the MAG inventory for early life. The MAGIC data entries and annotations are available at https://github.com/ohmeta/MAGIC and https://zenodo.org/doi/10.5281/zenodo.10369093. The code for the generation of prokaryotic MAGs and viral MAGs from raw sequencing reads is available at https://github.com/ohmeta/metapi. A tutorial for using MAGIC in the Phanta pipeline is available at https://github.com/ohmeta/MAGIC. Study details have been published in the reputable journal *Cell Host Microbe* [60]. In the next phase, we aim to double the number by adding samples from MOMMY as well as newly available public datasets.The MAGIC database^43^, therefore, not only recovers previously uncharted genomic information but also enables comprehensive characterization of the dynamics of early‐life microbiomes, identification of keystone species, and strain‐level study of target species. This database will be complementary to our prospective mother‐baby cohort, which we have collected over 58,000 biological samples (stool, serum, urine, vagina swab, buccal swab) and 25,000 web‐based clinical metadata based on validated questionnaires from parents and their infants at multiple time points in the pre‐, peri‐ and postnatal period. This exemplifies that our comprehensive databases can provide significant benefits to the industry, particularly startups and companies involved in diagnostic biomarker development for early‐life.(iv)
*
**MOMMY ‐ FA: The Impact of Food Additives on Maternal and Child Health Outcome**
* Accumulating evidence suggests that food additives can lead to altered gut microbiome composition [25, 26]. Yet the impact of food additive intake on early life gut microbiome and prenatal health has not been explored. We have developed and validated a food frequency questionnaire used to estimate additive intake over the preceding 12 months for the parents, which is collected at baseline, postnatal months 6 and 18. These questionnaires were developed to suit specific study regions by taking into consideration the dietary habits of the population living in that region. In brief, the questionnaire addresses intake frequency and amount of 26 food lists over the past 12 months. The food lists were created based on “Codex General Standard for Food Additives” food sub‐categories that contain additives of interest. Maximal exposure to nine food additives, namely three emulsifiers (CMC, carrageenan [CRN], and P80), three sweeteners (aspartame [ASP], saccharin [SAC], and sucralose [SUC]), and three humectants, preservatives, or coloring additives (aluminosilicate [AlSiO], sulfites [X(SO_2_)], and titanium dioxide [TiO_2_]) were assessed and estimated in mg/year based on the regional maximal permissible level (MPL) of additives in each food list, or where MPL does not exist, based on concentration data from the literature. We also established a mass‐spectrum (MS) based food additive levels measurement in different biological samples, including urine, serum, and stool.In a subgroup of pregnant women recruited to the MOMMY inception cohort, we will conduct a separate investigation into the potential impact of food additives. In MOMMY‐FA, the impact of food additives intake on two common perinatal diseases, GDM and offspring large for gestational age (LGA), and gut microbiome composition at late pregnancy will be assessed. Maternal stool collected at MG3 and infants' stool samples from birth till 1‐year‐old will be used to assess the potential transmission variance among different food additive intake groups. In the MOMMY cohort, using semi‐quantitative questionnaires (parental current and past food additive intake) and mass‐spectrum (MS) based food additive levels measurement in different biological samples, we are able to unravel the cross‐generational health impairment of food additives and whether it involves reforming the parental and postnatal gut microbiome.By observing the contribution of food additives on perinatal health and gut microbiome composition, we can develop more effective recommendations to promote healthy growth and development in infants and young children.(v)
*
**MOMMY ‐ COVID: Impacts of COVID‐19 Pandemic on Early Life Gut Microbiome**
*
The development origins of health and disease (DOHaD) hypothesis suggests that adverse exposure during early life, particularly in utero, may substantially influence later‐life health and disease status [61]. Analogous to DOHaD, the early life, especially the first 1000 days (from conception to 3 years of age) of life, is critical for gut microbiota establishment and development. The above evidence leads us to propose the hypothesis that the gut microbiome may be a key component contributing to the DOHaD concept [62]. Notably, MOMMY was established in Sep 2019 and “perfectly” experienced the COVID‐19 pandemic from 2020 to 2023. The COVID pandemic, as a natural experiment, provides a unique opportunity to examine the impact of early‐life adverse exposure on the adult and later‐life gut microbiota and the role of gut microbiota in the DOHaD. MOMMY‐COVID provided the unique opportunity to assess the effect of increased hygiene standards on early gut microbiome maturation. These insights will underscore the importance of considering the microbiome when evaluating hygiene measures and the need for future research to ascertain the role of the gut microbiome in disease development. Study details have been published in the reputable journal *Gut Microbes* [63].(vi)
*
**MOMMY ‐ GDM: Early Life Microbial Determinants in Gestational Diabetes Mellitus (GDM)**
* GDM, one of the most common gestational complications, increases the risk of long‐term complications in the mother, especially obesity, impaired glucose metabolism, and cardiovascular disease [64]. GDM can increase the risk of infant complications as well, such as neurodevelopment disorders and obesity [65, 66]. In MOMMY‐GDM, in this study, we investigated the gut microbiome profile of mothers during pregnancy and infants during the first year of life from a large‐scale longitudinal cohort of 264 mother‐baby dyads with 1566 total metagenomic sequence stool data in Hong Kong. We identified several maternal bacteria features associated with GDM status and glycemia levels during whole gestational periods. To our knowledge, this pioneering study identified that GDM is deeply fingerprinted on the gut microbiome of male offspring up to 12 months of life. Male infants born to GDM mothers have different gut microbiome, which associates with larger head circumference growth. Our new findings suggested the maternal prenatal gut microbiome was relevant to the children's neurodevelopment in the first year of life. However, the impact of GDM on offspring neurodevelopmental sex differences should be considered not only for brain damage but also for brain protection. Future research is necessary to understand the long‐term consequence of over‐growth in these infants and whether microbiota modulation serves as a potential approach to mitigate and prevent these risks. Study details have been published in the reputable journal *Cell Host & Microbe* [67].(vii)
*
**MOMMY ‐ IBD: The Impact of Food Additives on Gut Microbiota and Inflammatory Bowel Disease**
* IBD, including conditions like Crohn's disease (CD) and ulcerative colitis (UC), is characterized by chronic inflammation of the gastrointestinal (GI) tract, and its incidence and prevalence are increasing globally [68]. Factors such as maternal smoking, diet, antibiotics, and breastfeeding during early life can impact the risk of IBD through the gut microbiome [69, 70]. However, there is a dearth of prospective human studies investigating the relationship between maternal diet, microbiome, and IBD. The consumption of ultra‐processed foods and food additives has become increasingly common in modern diets [23]. Despite preclinical evidence, no human studies have yet examined the impact of maternal intake of food additives in mothers with IBD on the microbiome of their infants [71]. This multi‐center cohort study therefore provides an unprecedented opportunity to test the hypothesis that maternal food additive intake impacts the maternal gut microbiome, potentially affecting themicrobiome/inflammation status of their offspring up to 6–7‐year‐old. In MOMMY‐IBD, in the short term, we will focus on exploring the impact of diet on gut microbiota and subsequent host immune dysfunction that underlies mechanisms of gut inflammation in early life [72, 73]. Our long‐term goal is to modulate the intestinal microbiome with novel human‐derived bacteria consortia and dietary interventions to inhibit maternal inflammatory and immune pathways for the prevention of IBD. We will perform multi‐level immune profiling on infant stool and blood samples to capture both mucosal (stool samples) and systemic (blood samples at 4‐year‐old postnatal) immune responses. From stool samples, we will measure a panel of immune mediators using multiplex immunoassays. This will include key cytokines, such as pro‐inflammatory markers and immunoglobulin A (IgA), fecal calprotectin and lipocalin‐2 (LCN2) [74, 75, 76]. From blood samples, plasma cytokine and immune cell phenotyping (flow cytometry) will be performed by peripheral blood mononuclear cells (PBMCs) to characterize key cell populations (e.g., T‐regulatory cells (Tregs), Th1, Th2, Th17 cells, B cells, and innate immune cells). Three core pillars of our research directions: (A) Deciphering crosstalk and mechanisms of diet‐intestinal microbiota in the immunopathogenesis of IBD in early life; (B) Dissecting diet additives' impact on host early immunity development in infants born to IBD and healthy mothers; (C) Modulation of intestinal microbiota with novel bacteria consortia‐secreting immunomodulatory metabolites that target inflammation.(viii)
*
**MOMMY ‐ ATOPY: Childhood Allergy and the microbiome – precision health for life**
* Eczema causes substantial physical and psychosocial morbidities in these victims, and the current mainstay treatments with corticosteroids and other anti‐inflammatory drugs are associated with local and systemic adverse effects [77]. The early‐life gut microbiome is associated with the development of allergic diseases in children, including eczema, wheezing (asthma), and allergic sensitization. Among these allergic diseases, eczema affects up to 20% of children and represents one of the earliest manifestations of the atopic march [78, 79]. Therefore, it is important to identify the factors affecting eczema development, especially in Chinese children, who showed the highest incidence rate of eczema in the first year of life among other ethnic groups.In this MOMMY ‐ ATOPY, the incidence of eczema within 1‐year‐old (up to July 2023) is around ≈13% (156/1200 subjects). Leveraging the ongoing follow‐up of the MOMMY inception cohort, these estimations highlight the potential of MOMMY‐ATOPY for future prospective studies elucidating the role of the microbiome in pediatric allergic disease. Taking advantage of the allergy‐related clinical data collected systematically and prospectively, we will conduct a longitudinal nested case‐control study of atopic diseases across the first 6 years of life. Estimation of sample size: The relative microbiota maturity in our previous studies was used for sample size calculation. Relative microbiota maturity was defined as the predicted microbiota age of the infant minus the microbiota age of healthy infants at the same chronological age, as determined by the smoothing spline. Based on our pilot data, we assume an absolute difference of 5.1 (with SD of 18.6) for relative microbiota maturity between infants with or without eczema. A sample size of 220 in each group can detect this effect size with 80% power and two‐sided 5% type I error for a two‐sample *t*‐test. According to the accumulative 20% prevalence of atopic diseases, 1100 consecutive infants will be recruited and assessed from the MOMMY inception cohort.Our specific objectives were to (i) characterize the development of the gut, skin, and nasopharyngeal microbiome in a Chinese birth cohort during the first 6 years of life; (ii) identify risk factors for atopic disease development from maternal, perinatal, fetal, and environmental variables; and (iii) identify gut, skin, and nasopharyngeal microbiome signatures for prevention and treatment of food allergy, atopic dermatitis, and asthma in pre‐school children. We will perform shotgun metagenomic sequencing for the fecal microbiome profile and 16S rRNA amplicon sequencing for the skin and nasopharyngeal microbiome profile. We expect to unveil the role of interaction between environmental factors and gut, skin, and nasopharyngeal microbiome in atopic diseases and identify gut, skin, and nasopharyngeal microbiome signatures for the management of food allergy, atopic dermatitis, and asthma in preschool children.(ix)
*

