### How to follow‐up and retain subjects in early life microbiome‐related birth cohort?

#### Follow‐up and retention strategies

Comprehensive strategies are employed to retain participants throughout the study. During the antenatal period, mothers can contact the research team for any pregnancy‐related issues, with unscheduled research visits arranged as necessary. Post‐delivery, mothers often have numerous questions regarding breastfeeding and their babies' health; therefore, a dedicated hotline is established to provide professional nursing advice. Additionally, we offer free health checks, including a skin prick test in year two and an eye test in year three. Regular seminars on topics such as healthy diet, autism, and eczema are organized for families. During these seminars, we inquire about the child's eating habits and provide brief on‐site consultations for any noticeable eating problems. Furthermore, children with concerning standard health check results between 1.5 and 3 years old are offered an in‐depth interview for early assessment of behavioral issues. Notably, we also provide a microbial report for all 1‐year‐old infants at the Hong Kong site, allowing parents to arrange a consultation with the research team if necessary.

Figure 2 shows study participant recruitment and follow‐up until 31st March, 2024. At this stage of recruitment, a total of 2805 mother‐baby pairs (Hong Kong: 1989, Foshan: 700, Kunming: 116) were recruited, with a drop rate of 9.5% (267/2805) had withdrawn consent for participation during antenatal period, with the following reasons: (1) Personal reasons (64.4%), (2) Termination of pregnancy (14.2%), (3) Refused or lost further follow‐up (8.2%), (4) Refused to provide specimens (7.9%), and (5) Baby and/or mother's health problems (5.6%). During the postnatal (at any time point from delivery to postnatal year three) period, a total of 363 mother‐baby pairs were withdrawn (15.2% 363/2394). Specifically, we reached a response rate (with sample/questionnaire collected) of (2198/2394, 91.8%) at trimester two, (2267/2394, 94.7%) at trimester three.

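### MOMMY-ATOPY takes its effect size from eczema but its case yield from any atopic disease, so at equal groups the stated 80% power needs about 19% cumulative eczema with no loss

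*Protocol article*

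**What the plan says.** All the sizing statements are in the article's section on MOMMY-ATOPY (Studies derived from MOMMY, item viii).

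- Design: "we will conduct a longitudinal nested case‐control study of atopic diseases across the first 6 years of life".
- Effect size: "we assume an absolute difference of 5.1 (with SD of 18.6) for relative microbiota maturity between infants with or without eczema".
- Group size (t-test on two independent groups): "A sample size of 220 in each group can detect this effect size with 80% power and two‐sided 5% type I error".
- Conversion to a recruitment target: "According to the accumulative 20% prevalence of atopic diseases, 1100 consecutive infants will be recruited and assessed from the MOMMY inception cohort".
- Observed rate: "the incidence of eczema within 1‐year‐old (up to July 2023) is around ≈13% (156/1200 subjects").

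The same section puts 20% as the upper end of the share of children affected by eczema. It names food allergy, atopic dermatitis and asthma as target conditions. It gives no allowance for loss to follow-up. Elsewhere, under Follow-up and retention strategies, the article reports that between delivery and year three 363 mother-baby "pairs were withdrawn (15.2% 363/2394").

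**The concern.** The calculation has two steps, and they refer to different children. The first step finds how many infants with eczema are needed to detect a maturity difference estimated for eczema. The second finds how many infants must be assessed to obtain that number, but uses the prevalence of a wider group of diseases. The steps join up only if one of two things is true: eczema alone reaches nearly the full 20%, or children with other atopic diseases but no eczema show the same 5.1 difference. The section gives no pilot estimate for the second, and for the first it offers only an upper figure.

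If neither holds, the study either has fewer than 220 eczema cases, or makes up the number with cases to which the pilot effect size does not apply. In both situations the stated power is not secured, and a null result on microbiota maturity would be harder to interpret than the plan implies.

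**Working it through.** **Inputs, all from the MOMMY-ATOPY section unless noted.** Difference 5.1; SD 18.6; two-sided 5%; 220 per group; 1100 infants; 20% cumulative atopic disease; 13% eczema by age 1 (156/1200). From Follow-up and retention strategies: 15.2% postnatal withdrawal (363/2394), used only as an illustration of loss.

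**Step 1: reproduce the plan.** The standardised difference is 5.1/18.6 = 0.274. The normal approximation for 80% power is

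n = 2 × (1.960 + 0.842)² × (18.6/5.1)² ≈ 209 per group,

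and the t-test needs 210. With 220 per group the t-test has 81.8% power. The recruitment step is 220/0.20 = 1100. Both stated figures therefore reproduce. The 220 exceeds the minimum by about 5% (209/0.95 = 220), but the article does not say whether that margin is meant for loss.

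**Step 2: the eczema rate that the plan needs.** With equal groups, 210 cases out of 1100 is 210/1100 = 19.1%, with no loss. If 15.2% were lost, the rate needed would be 210/(1100 × 0.848) = 22.5%, above the upper figure that the section gives for eczema.

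**Step 3: power at other eczema rates.** The approximation is

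power ≈ Φ( 5.1 / [18.6 × √(1/n₁ + 1/n₀)] − 1.96 ).

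For 143 vs 143 this is Φ(5.1/2.200 − 1.96) = Φ(0.36) = 64%. The table gives t-test results, which agree with the approximation to within half a percentage point.

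| Cumulative eczema among 1100 | Cases | Controls | Power |
|---|---|---|---|
| 13% (observed by age 1; lower bound) | 143 | 143 | 64% |
| 13% | 143 | 220 (as planned) | 72% |
| 13% | 143 | 957 (all non-cases) | 86% |
| 15% | 165 | 165 | 70% |
| 20%, 15.2% lost | 187 | 187 | 75% |
| 20%, no loss | 220 | 220 | 82% |
| 20%, no loss | 220 | 880 (all non-cases) | 95% |

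Cases are rate × 1100: 0.13 × 1100 = 143, 0.15 × 1100 = 165, 0.20 × 1100 = 220, and 220 × 0.848 ≈ 187. Non-cases are 1100 − 143 = 957 and 1100 − 220 = 880.

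**Step 4: controls needed at the lower bound.** With 143 cases, 2.7 controls per case gives 79.8% and 2.8 gives 80.2%. About 400 controls (143 × 2.8) would therefore restore 80%.

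All figures assume equal SDs in the two groups and no information lost or gained through matching.

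**The case against.** The strongest reply is that nothing has been miscalculated and that 13% and 20% do not conflict. The 13% is eczema diagnosed within the first year. The 20% is cumulative, covers all atopic disease, and serves a study that follows children for six years. Eczema will accrue after age 1, and the section's own upper figure for eczema is also 20%. A shortfall of cases would not remove controls either, since 1100 infants leave 957 non-cases even at 143 cases. This reply stands as far as it goes. It makes 143 a lower bound on the yield before loss, not a forecast.

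A reader might therefore infer too much: that the study's power simply is 64%. The documents do not support that. It would require cases to be restricted to first-year eczema, which the plan does not say, and the planned 220 controls to be cut to 143, which it does not say either. A reader might also take 15.2% off the 143 cases. That is not justified: the figure is withdrawal at all sites up to year three, whereas the 13% is already an observed first-year count, and later withdrawal does not undo a diagnosis already made. Nor is there any basis for assuming that non-eczema atopic cases have no maturity difference at all; the article is silent on their effect.

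The reply does not remove the mismatch between the two steps. It also does not show that eczema will reach about 19%, which the equal-group design needs.

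**Conclusion.** The point holds as a mismatch of case definitions with little margin, not as an arithmetic error. Taken as written, with equal groups, 80% power depends on about 210 eczema cases: about 19% cumulative eczema, no loss, and a section that offers 20% only as a maximum. Between the observed first-year rate and that maximum, equal-group power runs from 64% to 82% without loss. Keeping the planned 220 controls lifts the lower end to 72%. If the full 20% is reached but losses match the cohort's 15.2%, equal-group power is about 75%.

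The loss figure is an assumption for this sub-study. It pools all three sites, while the inception cohort is described as 1200 Hong Kong families followed to the first year. Some of that loss may already have occurred, and follow-up to age 6 may add more. The final eczema rate at age 6 is not known from the article, so the power statement should be conditional on it.

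**What to change.** 1. Use the same case definition for the effect size and for the case yield. Since the pilot contrast is eczema, size the maturity comparison on eczema and keep the other atopic diseases as separate outcomes, without carrying the 5.1 difference over to them.
2. Replace the single figure of 220 with a range of expected eczema cases, about 143 to 220, give the power for each end, and say what loss has been assumed.
3. For the stool maturity endpoint, compare cases with all available non-cases among the 1100 in place of an equal-size group. Without loss this gives 86% at 143 vs 957 and 95% at 220 vs 880.

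The cost is mostly wording and some extra analysis. The section on the inception cohort reports more than 10,000 stool samples already sequenced, so much of the control data should be in hand, though some extra sequencing may be needed. The skin and nasopharyngeal 16S comparisons may have to stay on a smaller control set; if so, their power should be stated separately.
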